## Abstract

**Background:**

Upper limb dysfunction seriously affects the ability of stroke patients to perform activities of daily living. As a popular exercise therapy, Tai Chi may become an alternative intervention. However, the neurophysiological mechanism by which Tai Chi improves upper limb dysfunction in stroke patients is still unclear, which limits its further promotion and application. Therefore, conducting a strict randomized clinical trial is necessary to observe how Tai Chi affects upper limb dysfunction in stroke patients and to explore its neurophysiological mechanism.

**Methods/design:**

This report describes a randomized, parallel-controlled trial with distributive concealment and evaluator blinding. A total of 84 eligible participants will be randomly assigned to the Tai Chi group or the control group in a 1:1 ratio. The participants in the Tai Chi group will receive 4 weeks of Tai Chi training: five 60-min sessions a week for a total of 20 sessions. The participants in the control group will not receive Tai Chi training. Both groups will receive medical treatment and routine rehabilitation training. The primary outcome measure is the mean change in the Fugl-Meyer Assessment Upper Extremity (FMA-UE) scale score between baseline and 4 weeks; the secondary outcomes are the mean changes in kinematic characteristics and the Wolf Motor Function Test (WMFT) and Stroke Impact Scale (SIS) scores. In addition, the corticomuscular coupling level and near-infrared brain functional imaging will be monitored to explore the mechanism by which Tai Chi improves upper limb function of stroke patients.

**Discussion:**

This randomized controlled trial will examine the effectiveness of Tai Chi in stroke patients with upper limb dysfunction and explore the neurophysiological mechanism. Positive results will verify that Tai Chi can improve upper limb function of stroke patients.

**Trial registration:**

Chinese Clinical Trial Registration Center, ChiCTR2200061376 (retrospectively registered). Registered June 22, 2022. http://www.chictr.org.cn/listbycreater.aspx. Manuscript Version: 3.0 Manuscript Date: October 10, 2023.

**Supplementary Information:**

The online version contains supplementary material available at 10.1186/s13063-023-07743-w.

## Background

Upper limb motor dysfunction after stroke is a significant problem that affects the quality of life of stroke patients [1]. Research shows that about 85% of stroke patients have upper limb dysfunction when they first get sick. Approximately 15% of these patients recover hand function to about 50% of their original level, while only 3% of patients recover hand function that is > 70% of their original level [2]. Upper limb function is of great significance to individuals and society because the upper limb motor ability is necessary for activities of daily living and affects quality of life [3].

Studies have confirmed that Tai Chi has a positive clinical effect on upper limb dysfunction in stroke patients. A meta-analysis showed that upper limb rehabilitation training is one of the most widely used and effective measures for patients with upper limb dysfunction after stroke. Some scholars [4] have evaluated the efficacy of Tai Chi in treating post-stroke upper limb dysfunction and have systematically reviewed the relevant randomized controlled trials. The results support the conclusion that Tai Chi combined with upper limb rehabilitation training is significantly better than upper limb rehabilitation training alone to treat post-stroke upper limb dysfunction. Indeed, Tai Chi combined with rehabilitation training significantly improves upper limb function compared with control treatment [5].

Coupling of the sensorimotor frontal-parietal network and muscle activation patterns is an essential mechanism for functional recovery of upper limbs. Bilateral coupling between the ascending and descending cortex and muscle in the sensorimotor control circuit is weakened in stroke patients, resulting in abnormal upper limb muscle coordination and movement patterns as well as compensatory movement [6–8]. When the elbow of a stroke patient moves, β and γ functional corticomuscular coupling (FCMC) of the anterior deltoid and brachial muscles change. A decrease in FCMC in the biceps brachii and an increase in FCMC in the deltoid muscle are related to a reduction in elbow flexion and excessive abduction of the shoulder joint [9]. Therefore, abnormal movement patterns in stroke patients, including slow movement, poor fluency, and greater movement variability, lead to compensatory trunk movement [10, 11].

Researchers have also found that enhanced coupling of the sensorimotor frontal-parietal cortex and muscle activation patterns is closely related to upper limb function recovery. Participants with high resting-state functional connectivity (rsFC) within and between motor networks—the contralateral primary motor cortex (M1) and the ipsilateral supplementary motor area SMA)—and frontal-parietal networks—between the dorsolateral prefrontal cortex (DLPFC) and the medial ventrolateral prefrontal cortex—have better hand function [12]. The functional connectivity (FC) of the ipsilateral premotor cortex (PMC) and the frontal-parietal region (bilateral precuneus and the DLPFC) are positively correlated with motor function. Compared with the healthy side, the FC of the ipsilateral somato-motor/sensory network (SMN) increases with bilateral frontal lobe (DLPFC) and the ipsilateral posterior parietal cortex (Pcu) during hand movement. The FC of the ipsilateral PMC and frontal-parietal region (bilateral Pcu and contralateral DLPFC) is positively correlated with motor function [13]. The motor frontal-parietal connection may be related to the neural processes related to motor execution and may be a potential biomarker for motor recovery after stroke [14].

Coupling of the sensorimotor frontal-parietal cortex and the muscle may be an essential mechanism by which Tai Chi improves upper limb function. Studies have confirmed that Tai Chi activates sensorimotor function, the frontal-parietal lobe, and other brain regions in healthy individuals. Tai Chi improves the functional integration of motor and sensory areas in ordinary people and optimizes the function of the attention control area (DLPFC) [15]. Tai Chi promotes the functional connection of the motor area (MC), the prefrontal lobe (PFC), and the occipital lobe (OL) in ordinary people. Compared with the control group, people who received Tai Chi training had greater brain activity, including in the MC, PFC, and OL, during the rest and exercise states, enhancing the synergy of neural activities in bilateral brain regions [15, 16]. These findings prove that Tai Chi exercise activates the frontal-parietal lobe region [17]. Researchers have also found that Tai Chi promotes activation of upper limb muscles and improves proprioception. That is, it promotes downward motor output and upward sensory input. Tai Chi can activate upper limb muscles, such as the anterior deltoid and triceps brachii. Older adult Tai Chi practitioners show greater activation of the anterior and middle deltoids in reaching objects and faster reaction and exercise times [18]. Tai Chi improves the proprioception of stroke patients, indicating that the sensorimotor circuit is regulated by Tai Chi [19]. Tai Chi improves the movement pattern, increases shoulder movement, and improves the ability of movement control [20]. In addition, relevant studies have reported on how Tai Chi improves upper limb control in older adults. The results have shown that compared with control individuals, Tai Chi practitioners have a better response and exercise time, hand-eye coordination, and upper limb movement control in more complex tasks [21]. In addition, rehabilitation training promotes the coupling of the sensorimotor frontal-parietal cortex and upper limb muscle patterns to promote regular muscle coordination and reduce compensatory movement [22–28].

Based on the available data, Tai Chi improves upper limb function of stroke patients. In stroke patients, the abnormal two-way coupling of the sensorimotor frontal-parietal network and upper limb muscle activation pattern leads to abnormal upper limb muscle coordination and movement. Tai Chi can activate brain areas related to sensorimotor function and the frontal-parietal lobe, improve the activation of upper limb muscles in stroke patients, and promote sensory input. In this study, stroke patients with upper limb dysfunction will be treated with Tai Chi, and the changes in their kinematic characteristics after Tai Chi training will be evaluated based on a markless sensing technique to distinguish between recovery and compensation. This study will use multimodal Kinect, functional near-infrared spectroscopy (fNIRS), electroencephalography (EEG) and surface electromyography (EMG). Closed-loop structure and graph theory will be used to analyse the results and to clarify the cortical-muscular network functional reorganization mechanism of Tai Chi on upper limb function.

At present, domestic and foreign studies have explored the impact of different rehabilitation interventions on the brain-muscle coupling of upper limb function in post-stroke patients, such as botulinum toxin combined with rehabilitation [29], virtual reality muscle computer interface [22], transcranial direct current stimulation [30] and transcranial magnetic stimulation [31]. However, no literature reports the bidirectional interaction and reorganization mechanism of post-stroke patients’ cortical and upper limb muscle networks after Tai Chi training. Previous studies on the effects of Tai Chi after stroke have mainly focused on the overall efficacy of upper limb function and neural excitability. The results of this trial will help provide a theoretical basis for the clinical optimization of Tai Chi to improve upper limb motor function in post-stroke patients.

## Methods/design

### Study design

A randomized, single-blind, parallel-controlled trial will be conducted to evaluate the effectiveness and neural mechanism of traditional Tai Chi training in stroke patients with upper limb dysfunction. The framework of this trial is a superiority trial design. The evaluators and data analysts will be blinded regarding the treatment. A total of 84 eligible participants will be randomly assigned to the Tai Chi group or the control group in a 1:1 ratio. Members of the Tai Chi group will receive 4 weeks of Tai Chi training five times a week, with each session lasting for 60 min (a total of 20 sessions). Participants in the control group will not receive Tai Chi training. Both groups will receive medical treatment and routine rehabilitation training. The primary and secondary outcomes will be measured at baseline and 4 weeks (the end of intervention). This study will use the SPIRIT reporting guidelines [32] (see Additional file 3 for more details). The flow chart of the research design is shown in Fig. 1, and the enrolment, intervention and assessment schedule is shown in Fig. 2. Additional file 4 shows additional details.

**Fig. 1 Fig1:**
[figure not shown]
Flow diagram of the participants. Abbreviations: EEG, electroencephalography; EMG, electromyography; fNIRS, functional near-infrared spectroscopy; FMA-UE, Fugl-Meyer Upper Extremity; Kinect, Azure Kinect kinematic analysis; MAS, Modified Ashworth Scale; SIS, Stroke Impact Scale; WMFT, Wolf Motor Function Test

**Fig. 2 Fig2:**
[figure not shown]
SPIRIT figure showing the enrolment, intervention, and assessment schedule. Abbreviations: EEG, electroencephalography; EMG, electromyography; fNIRS, functional near-infrared spectroscopy; FMA-UE, Fugl-Meyer Upper Extremity; Kinect, Azure Kinect kinematic analysis; MAS, Modified Ashworth Scale; SIS, Stroke Impact Scale; WMFT, Wolf Motor Function Test

### Sample size estimation

This trial will observe the effects of Tai Chi on upper limb function of post-stroke patients. When calculating the required sample size using the Gpower V.3.1.9.2 software, the Fugl-Meyer Assessment Upper Extremity (FMA-UE) scale served as the primary outcome measure. Based on a published study [33], the FMA-UE scores of stroke patients in the Tai Chi and control groups after intervention were 60.50±2.19 and 59.14±1.77 points, respectively. According to these results, a sample size of 64 participants would be sufficient to detect the target effect size (0.6830377) with a type 1 error of 5% (*α* = 0.05) and 80% power (*β* = 0.20). Assuming a dropout rate of 20%, a total of 84 participants are necessary, with 42 participants in each group.

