#### Inclusion criteria

To be eligible to participate in the study, each participant must meet the following criteria:Meet the diagnostic criteria of ‘stroke’ in the diagnostic essentials of various cerebrovascular diseases adopted at the Fourth National Cerebrovascular Disease Academic Conference in 1995 and confirmed by head computed tomography or magnetic resonance imaging;The first stroke occurred between 2 weeks and 6 months prior to commencing the study;Unilateral cortical lesion (left or right hemisphere) or subcortical lesion involving the motor pathway;The muscle strength of the upper limb of the affected side is ≥ 3 and muscle tone is ≤ 2 based on the Modified Ashworth Scale (MAS);Right-handedness before stroke;Age between 50 and 70 years;Blood pressure stable and below 160/100 mmHg;A Mini-Mental State Examination (MMSE) score of > 17 points for illiterate participants, > 20 points for participants with a primary school education, and > 24 points for participants with a middle school and above education;Brunnstrom stage ≥ IV in the affected upper limb;Standing balance ≥ level 2, the ability to stand independently for more than 5 min, and the ability to walk independently for more than 6 m;Willing to sign the informed consent form and understand, accept, and implement the rehabilitation guidance.

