#### Primary outcome measures

The primary outcome measure is the change in the FMA-UE scale score from baseline to the end of the 4-week intervention. The FMA-UE scale includes 33 items divided into four subscales (arm, wrist, hand, and coordination), each scored on a 3-point sequential scale [37]. Scoring is based on performing independent actions inside and outside the synergy pattern. The maximum score of 66 corresponds to undamaged motor function. The FMA-UE scale is often used to classify the severity of stroke injury, and the scale shows good reliability and validity. A FMA-UE score between 32 and 57 indicates moderate upper limb injury and an FMA-UE score between 58 and 65 indicates mild injury of the contralateral arm. FMA-UE sensation (0–12), passive range of motion, and pain (0–24) will also be assessed.

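### The effect size comes from post-intervention FMA-UE scores, not from change; no stated SD supports it for this endpoint and intake, and 64 participants do not give 80% power even on the stated inputs

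*Protocol article*

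**What the plan says.** In the protocol article, Sample size estimation takes its planning figures from a single published study: "the FMA-UE scores of stroke patients in the Tai Chi and control groups after intervention were 60.50±2.19 and 59.14±1.77 points, respectively". From these it derives an effect size of 0.6830377 and concludes, for a 5% type 1 error and 80% power, that "a sample size of 64 participants would be sufficient". It then states: "Assuming a dropout rate of 20%, a total of 84 participants are necessary, with 42 participants in each group". Whether the test is one- or two-sided is not stated.

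Primary outcome measures defines a different quantity: "The primary outcome measure is the change in the FMA-UE scale score from baseline to the end of the 4-week intervention". The same section sets the scale maximum at 66 and gives the severity bands: "A FMA-UE score between 32 and 57 indicates moderate upper limb injury and an FMA-UE score between 58 and 65 indicates mild injury".

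The Inclusion and Exclusion criteria contain no FMA-UE minimum or maximum. Upper-limb severity is limited only indirectly, by muscle strength of at least 3, a Modified Ashworth score of at most 2 and "Brunnstrom stage ≥ IV in the affected upper limb".

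Statistical analyses plans a t test or Mann-Whitney test between groups at each time point, and a linear mixed model with a group × time interaction.

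**The concern.** The SD that fixes the effect size belongs to scores measured once, after treatment. The endpoint is a difference between two measurements, and its SD also depends on the baseline SD and on the correlation between baseline and follow-up. The article gives neither, and it shows no sensitivity range.

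Nor does anything in the eligibility criteria tie this trial's score spread to the source study's SD of about 2 on a 66-point scale. The power claim therefore rests on a figure that is not justified for the analysed quantity or for this intake.

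At stake is the reading of a null result. A reader told that the trial had 80% power would take it as evidence against a difference of the planned size. That is sound only if the SD is as small as assumed. Separately, the step from the effect size to 64 participants should be checked on its own terms.

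**Working it through.** **Inputs from the article.** Post-intervention means 60.50 and 59.14; SDs 2.19 and 1.77; α = 0.05; power 80%; 1:1 allocation; 64 evaluable; 20% dropout; 84 randomised. A two-sided test is my assumption.

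**1. Effect size.** Difference = 60.50 − 59.14 = 1.36. Pooled SD = √[(2.19² + 1.77²)/2] = 1.991. d = 1.36/1.991 = 0.6830. This reproduces the stated figure, so the effect size rests wholly on post-intervention scores.

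**2. Sample size.** Power of the two-sample t test comes from the noncentral t distribution with noncentrality d√(n/2), n per arm, and 2n − 2 degrees of freedom.

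- 64 evaluable (32 per arm): 76.7%.
- 84 × 0.8 = 67.2 evaluable (33.6 per arm): 78.8%. With whole numbers, 33 against 34, it is 78.6%.
- 70 evaluable (35 per arm): 80.4%, the smallest equal allocation that reaches 80%.
- 84 evaluable (no loss): 87.1%.

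Other readings do not return 64 at 80% power: two-sided normal approximation 68, one-sided t test 56, one-sided normal approximation 54.

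**3. Dropout.** 64/0.8 = 80, not 84. 70 × 1.2 = 84, which matches the stated total, but inflating by multiplication does not leave 70 after a 20% loss. 70/0.8 = 87.5, so 88.

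**4. Dependence on the SD.** With about 67 evaluable, the detectable standardised difference at 80% power is about 0.69 (0.694 at 33.6 per arm, 0.695 at 33 against 34). For 1.36 points the SD may then be at most 1.36/0.694 = 1.96. The limit is 1.91 with 64 evaluable and 2.20 with all 84. The documents give no SD of change, so the SDs below are assumptions.

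| Assumed SD of analysed quantity | Power for 1.36 points, about 67 evaluable | Difference detectable at 80% power (points) |
|---|---|---|
| 2 | 78% | 1.4 |
| 2.5 | 59% | 1.7 |
| 3 | 45% | 2.1 |
| 4 | 28% | 2.8 |
| 5 | 20% | 3.5 |
| 6 | 15% | 4.2 |

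At SDs of 2.5, 3 and 4, 80% power for 1.36 points would need 110, 156 and 274 evaluable participants.

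**5. From post-score SD to change SD.** With equal SDs at both visits and correlation r, SD of change = SD × √[2(1 − r)]. Taking SD = 1.99 and 67 evaluable:

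- r = 0.3: SD of change 2.36, power 64%.
- r = 0.5: SD of change 1.99, power 79%.
- r = 0.7: SD of change 1.54, power 94%.

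So the mismatch has no fixed direction. A wider score spread matters more. An assumed score SD of 6 gives an SD of change of 2.68 and 53% power at r = 0.9, and 1.90 and 82% at r = 0.95.

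**The case against.** The strongest reply is that the article powers for a standardised effect of 0.683, and power for a standardised effect does not depend on the SD. That is correct, and the middle column of the table holds the raw difference at 1.36 while only the SD grows. Patients with more room to improve might show a larger difference, so those powers are conditional scenarios and not forecasts. What remains is that 0.683 was obtained as 1.36/1.99 from another quantity, and nothing shows that it carries over to change in this intake.

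A second reply is that planning on post-scores can be conservative. This also stands: with equal SDs and a correlation above 0.5, change has the smaller SD. A reader might infer that using post-scores inflates the power, and the documents do not support that.

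A third reply is that the planned t test at each time point compares post-scores, so a post-score SD is the right kind of quantity. The defined primary outcome is nonetheless change, and the size of the SD in this intake would still be unsupported.

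Other tempting readings go further than the documents allow:

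- **A source cohort confined to the mild band, set against a wider intake here.** The source study's entry criteria and baseline scores are not shown. Even after treatment, about 26% of a normal control arm with mean 59.14 and SD 1.77 would fall below 58.
- **Scores in this trial spread evenly over 32 to 65.** Nothing in the documents supports this; the strength, tone and Brunnstrom criteria narrow severity.
- **Full-score entrants diluting the effect.** No listed criterion excludes a score of 66, but the study population is described as having upper limb dysfunction, and such entrants are conjecture.

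**Conclusion.** The point holds in a limited form. The effect size is taken from post-intervention scores, the endpoint is change, and the article gives no SD of change, no correlation and no FMA-UE range to connect the two.

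The arithmetic is also short on its own inputs. Two-sided, the shortfall is small: 3.3 percentage points at 64 evaluable and 1.2 at about 67, with 70 evaluable (88 randomised at 20% dropout) needed. It disappears if dropout is well below 20%, and it does not apply to a one-sided test, which the article does not state.

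The larger exposure is conditional. With 67 evaluable, 80% power for 1.36 points needs an SD of about 1.96 or less, and an SD of 3 would put power at 45% if the difference stays at 1.36. Whether the SD of change in this trial lies above or below 1.96 cannot be told from the documents, so they do not show that the trial is badly underpowered.

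**What to change.** Keep 84 randomised and restate Sample size estimation on the analysed quantity, for example:

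> With 84 randomised and 20% dropout, about 67 evaluable participants give 80% power (two-sided α = 0.05) for a standardised difference of 0.69 in change in FMA-UE. This is about 1.4 points if the SD of change is 2, 2.1 if 3, 3.5 if 5 and 4.2 if 6.

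Correct the 64: the stated effect size needs 70 evaluable, and 88 randomised if 20% are lost. State the sidedness.

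Then compare the assumed SD with the SD of change in participants already assessed at both visits, pooled without the A/B labels. This needs no unblinding. The pooled figure slightly exceeds the within-arm SD: with a true difference of 1.36 and a within-arm SD of 2, it is √(2² + 0.68²) = 2.11.

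The cost is a few sentences and one descriptive calculation on data already held. Eligibility, the sample size and the analysis stay as they are. The price is a less favourable statement in points if the SD proves larger than 2.

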### Randomization and allocation concealment

After baseline assessment, eligible participants will be randomly assigned to the Tai Chi group or the control group in a 1:1 ratio. Random assignment sequences will be generated by independent statisticians using the SAS 9.1 statistical software. Opaque, sealed envelopes will hide the randomization sequence, and participants will be managed by an independent research assistant who will know nothing about recruitment, evaluation, and intervention. The independent research assistant will inform the eligible participants of their assignment results by telephone.

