Effective connectivity (EC) analysis of the CLN is based on defining brain and muscle regions and ROIs. The basis for extracting ROIs from brain regions is that the brain map guides ROIs, and there are no overlapping regions to ensure the selection of functionally meaningful connected regions. The cortical reconstruction of the head model is used as the accurate geometric head model of the subjects. The EEG signals collected from the standard electrode leads of the international 10–20 system are represented on an accurate geometric model. First, the motor areas of the unaffected and affected sides are selected as ROIs, defined as Mu and Ma, respectively. The unaffected and affected somatosensory cortices are also considered to be ROIs, corresponding to Su and Sa, respectively. Finally, ROIs from unaffected and affected frontal and parietal regions are defined as Fu, FA, PAu, and PAa, respectively. For the muscle regions related to the two anatomical parts of the upper limb, according to the signals collected from the myoelectric electrodes on the affected side, the proximal (including the superior trapezius, the anterior deltoid, the posterior deltoid, the middle deltoid, the biceps brachii and the triceps brachii) and distal muscles (including the flexor carpi radialis and the extensor carpi radialis longus) of the upper limb are divided into two regions, which are defined as PM and DM. Based on the above 14 ROIs, the inflow index (IFI) and the outflow index (OFI) are used to determine the causal relationship between ROIs before and after training. To determine the difference in the average FcePDC value between the two groups in each frequency band before and after training, the FcePDC value calculated before training is defined as the baseline. The baseline changes are calculated by subtracting the baseline before training from the post-training values, and an independent-sample two-tailed *t*-test is performed to compare the changes between the two groups. In addition, repeated measures analysis of variance is used to test the statistical difference in the average FcePDC values in different information flow directions before and after training. Bonferroni correction is used to correct for multiple comparisons. The inter-group differences in network parameters (weighted clustering coefficient [C_W_] and weighted shortest path length [L_W_]) are tested with the Mann-Whitney *U* test. For EC analysis, the IFI and OFI values of ROI changes before and after training in the two groups are tested by paired two-tailed *t*-tests. The consistently paired *t*-test is used for the betweenness centrality parameter (BCX). The confidence level *α* is defined as 0.05.

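### The sample-size figures do not reproduce or agree: under a two-sided t test the stated effect size needs 70 evaluable participants, not 64, and 64 with 20% dropout does not give 84

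*Protocol article*

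**What the plan says.** The section Sample size estimation takes FMA-UE scores after intervention from a published study. The Tai Chi and control values "were 60.50±2.19 and 59.14±1.77 points, respectively". From these it derives a standardised effect size and concludes that "a sample size of 64 participants would be sufficient to detect the target effect size (0.6830377) with a type 1 error of 5" per cent and 80% power, using G*Power. The next sentence reads: "Assuming a dropout rate of 20%, a total of 84 participants are necessary, with 42 participants in each group".

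The section names neither the test nor its sidedness. Allocation is equal: participants are "randomly assigned to the Tai Chi group or the control group in a 1:1 ratio" (Randomization and allocation concealment). The only sidedness stated anywhere is for exploratory connectivity and network measures, for example where "an independent-sample two-tailed *t*-test is performed to compare the changes between the two groups" (Analysis of fNIRS, EEG, and EMG data). For the behavioural outcomes, Statistical analyses names Student's t test or the Mann-Whitney U test without saying whether it is one- or two-sided. The primary outcome is the change in FMA-UE from baseline to 4 weeks (Primary outcome measures).

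**The concern.** Effect size, alpha, power and allocation ratio are all given, so the evaluable number should follow from them, and the enrolled number should follow from the evaluable number and the dropout rate. Neither step works. The 64 is too small for a two-sided test and too large for a one-sided one, and 84 cannot be reached from 64 with a 20% allowance.

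At stake is the only justification given for the size of the trial. As written, the evaluable target, the power and the dropout allowance cannot all be true. A final evaluable count of 64 to 69 would be read as meeting the target at 80% power, whereas two-sided power would run from 76.7% to just under 80%.

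**Working it through.** **Inputs** (Sample size estimation unless noted): means 60.50 and 59.14; SDs 2.19 and 1.77; alpha 0.05; power 80%; dropout 20%; 1:1 allocation (Randomization and allocation concealment). Sidedness is not given, so both versions are computed.

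**1. Effect size (the plan's own figure).**
Pooled SD = √[(2.19² + 1.77²)/2] = √3.9645 = 1.9911.
d = (60.50 − 59.14)/1.9911 = 1.36/1.9911 = 0.68304.
This agrees with the stated 0.6830377, so any error comes after this step.

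**2. Evaluable number.** For a t test with n per arm, power comes from the noncentral t distribution with 2n − 2 degrees of freedom and noncentrality d√(n/2).

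| Test, alpha 0.05, 80% power | n per arm (t test) | Total (t test) | Total (normal approximation) |
|---|---|---|---|
| Two-sided | 34.63, so 35 | 70 | 68 |
| One-sided | 27.2, so 28 | 56 | 54 |

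None of these totals is 64.

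**3. Power at 64 (32 per arm).** Noncentrality = 0.68304 × √16 = 2.732. Two-sided power is 76.7%; one-sided power is 85.5%. Neither is the stated 80%.

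**4. From evaluable to enrolled, which does not depend on the test.**
- 64/(1 − 0.20) = 80.
- 64 × 1.20 = 76.8, so 77.
- Going from 84 to 64 is a loss of 20/84 = 23.8%.
- 84 less 20% is 67.2, not 64.

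**5. Where 84 could come from.** 70 × 1.20 = 84 exactly. Multiplying by 1.20 does not fully cover a 20% loss; dividing does: 70/0.80 = 87.5, so 88.

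**6. What 84 enrolled delivers (two-sided t test, d = 0.683).**

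| Evaluable | Loss from 84 | Power |
|---|---|---|
| 84 | 0% | 87.1% |
| 70 | 14/84 = 16.7% | 80.4% |
| 67.2 | 20% | 78.8% |
| 64 | 23.8% | 76.7% |

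With whole participants (33 and 34), power at 20% loss is 78.6%, and the standardised difference detectable with 80% power is about 0.69.

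**The case against.** The strongest reply is that nothing of substance changes. Enrolment is fixed at 84 throughout the article. At the planned 20% dropout, two-sided power is 78.8%, which is 1.2 points below target, and with no dropout it is 87.1%. This stands, and it keeps the point minor.

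The second reply is that 70 rests on a sidedness the section does not state. Under a one-sided test, 64 is indeed sufficient (85.5% power), and the 67 left after 20% loss exceeds it. This stands in part, and the two-sided assumption must be declared. It does not rescue the passage, because a one-sided calculation returns 56. The 64 can be reached by a one-sided t test at 85% power, which contradicts the stated 80%, or by a one-sided Mann-Whitney test at its minimum relative efficiency, which the section does not mention. Even then, 84 does not follow from 64.

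Several stronger readings are tempting, but the documents do not support them:
- A reader might infer that follow-up effort would stop once 64 are evaluable. Nothing makes 64 a stopping target. Data collection and management says that effort will be made to obtain follow-up data from participants who withdraw and are willing, and Statistical analyses plans an intention-to-treat analysis with multiple imputation.
- A reader might put a figure on the further loss of power if the Mann-Whitney test is used. That needs a relative efficiency, which depends on the shape of the distribution, and the article gives none.
- A reader might say that baseline adjustment makes up the shortfall. That needs a correlation between baseline and follow-up, which is not given.
- A reader might take 70 × 1.20 = 84 as proof that the software returned 70 and that 64 is a slip. It is a plausible explanation, but the section never mentions 70.

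**Conclusion.** The point holds as a minor correction of stated figures. Given a two-sided 5% t test, 80% power needs 70 evaluable participants, 6 more than stated, and 64 gives 76.7%. The mismatch between 64 and 84 needs no assumption about the test: a 20% allowance on 64 gives 80 or 77.

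The documents do not support the conclusion that the trial is materially underpowered. On the cited inputs, 84 enrolled keeps 80% power up to 16.7% dropout and falls about one point short at 20%.

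Two assumptions limit these figures. Two-sidedness is taken from convention. Every power value also uses SDs of post-intervention scores, whereas the primary outcome is change from baseline. The SD of change is not given, so these are corrections on the plan's own basis and not a certified power for the primary analysis.

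**What to change.** Revise Sample size estimation as follows:
- State the test and its sidedness.
- If it is a two-sided t test, replace 64 with 70 evaluable participants (35 per arm) for 80% power. If another test was meant, name it and give the number that it returns.
- Replace the dropout sentence: 84 enrolled (42 per arm) keeps 80% power up to 16.7% dropout; at 20% dropout about 67 remain, with about 79% power and a detectable standardised difference of about 0.69.
- Add that these figures are conditional on the cited post-intervention SDs, while the primary outcome is change from baseline.

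The cost is wording only. Enrolment stays at 84, and the power stated at 20% dropout becomes about one point less favourable. Keeping a full 80% at 20% dropout would take 88 enrolled, but a one-point gap does not call for it.
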